## Methods/design

### Study design

Our study design is consistent with CONSORT recommendations for RCTs, 2010 update [32] and extension for trials of non-pharmacological treatments [33]. Participants will be stratified by location and arthritis type and randomized 1:1 to receive either our program, or “usual care” as initiated by their physician and supplemented by printed material about work and arthritis. Participants will be followed for 5 years, the estimated time required, according to our power calculations, to observe a difference in work cessation similar to that in Allaire’s RCT [34]. After 2 years, analysis of our first primary outcome, at-work productivity, will be performed, along with an interim analysis of the second primary outcome, work cessation. If a significant difference in work cessation is observed between the two groups, the RCT will be terminated prematurely. Because of the nature of the intervention, participants cannot be blinded. Ethics approval was obtained from the University of British Columbia Research Ethics Board (H11-03527).

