### Randomization

Randomization will be stratified by study centre (3 levels) and type of arthritis (4 levels). In each stratum, we will use blocked randomization, with random and variable block sizes, to ensure optimal balance between trial arms, while avoiding the risk of study personnel ‘guessing’ the next allocation. Randomization will be performed centrally, in Vancouver; by the biostatistician (CG) using a customized program in the R programming language, after the study coordinator has confirmed eligibility and received informed consent. To ensure concealment of the randomization list from those making eligibility decisions, allocations will be available for one patient at a time.

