### Sample size and analysis

Sample size was calculated for the primary outcome requiring the largest sample, i.e. time to work cessation. It was performed with PASS software [42] for time-to-event analyses. We assumed 5 years of follow-up and a rate of work cessation of 12.77% per year in the control group, based on the 40% work loss observed in controls over 4 years in Allaire’s RCT of VRC [34], and assuming an exponential distribution of time to work loss. A sample size of 420 subjects (210 per group) completing the study is necessary for 80% power, a 2-tailed Cox model-based score test, equivalent to the logrank test, at alpha = 0.05, to detect a 35% relative risk reduction (HR = 0.65) in the intervention vs. control group, which was considered a minimally clinically important difference (MCID), and is moderately conservative compared to the 42% risk reduction observed in Allaire’s study (HR = 0.58, 95% CI:0.34-0.99) [34]. Assuming 20% loss to follow-up, we will recruit a total of 526 subjects (263 per group). This sample will ensure adequate power for our other primary outcome, at-work productivity.

Appropriate descriptive statistics will be used to measure baseline characteristics of the two groups. Analysis of treatment effectiveness will rely on intention-to-treat (ITT) approach, so that all patients initially randomized will be included in the analysis, regardless of their compliance or drop-outs.

For the analysis of our first primary outcome, at-work productivity measured as a continuous variable will be tested for normality using the Shapiro-Wilk test [43]. If normality assumption is rejected, an appropriate transformation (e.g. such as logarithmic) will be employed to obtain an approximately normal distribution. Next, an Analysis of Variance (ANOVA) will evaluate the effect of the intervention on WIS measures at 2 years, adjusting for the 12 strata and blocking. We will also consider an Analysis of Covariance model after inspection of the baseline values in both treatment arms for factors such as WIS score, duration of disease, physician providing RA care, age, gender and risk factors for WD. If differences at baseline are observed, we will consider them as covariates. Since the power of these analyses will likely be less than the original ANOVA, post hoc power analyses will be conducted if these appear to be clinically meaningful adjustments.

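### The primary WIS model always adjusts for randomization blocks but adjusts for baseline WIS only if imbalance is seen; if blocks are fixed effects and scores are missing, this costs some precision

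*Protocol article*

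**What the plan says.** Under Randomization, the protocol article states: "Randomization will be stratified by study centre (3 levels) and type of arthritis (4 levels"), which gives 3 × 4 = 12 strata. Within each stratum "we will use blocked randomization, with random and variable block sizes". Under Study design, participants are "randomized 1:1 to receive either our program" or usual care.

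Under Sample size and analysis, the 2-year WIS score is compared by ANOVA "adjusting for the 12 strata and blocking". Covariates, with baseline WIS among the candidates, are considered only after the baseline values have been inspected and only if differences appear. The same paragraph expects the covariate-adjusted analysis to have less power than the ANOVA.

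The section promises an intention-to-treat analysis of everyone randomized, including drop-outs. It says that power for at-work productivity is adequate but gives no WIS difference, standard deviation or power. The article does not say what the block sizes are, whether block is a fixed or a random effect, or how missing 2-year WIS is handled. These details can properly sit in a fuller document. They matter here only because the size of the effect depends on them.

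**The concern.** Permuted blocks are short runs of consecutive enrolments in a stratum. They keep the arms balanced and the next allocation hard to guess. The article gives no reason to think that block membership predicts WIS.

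If block is a fixed factor, which is the usual reading of a block term in an ANOVA, the nested blocks absorb the strata and treatment is compared only within blocks. The model then spends roughly 90 to 180 parameters for the block sizes considered below. Once scores are missing, some blocks become unbalanced. A block with only one arm observed says nothing about the treatment effect.

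Meanwhile baseline WIS, one parameter and a natural predictor of 2-year WIS, is left to an inspection for imbalance. So the large set of terms with no stated prognostic value is always in the model, and the single term likely to help is optional. Precision on a primary outcome is at stake.

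**Working it through.** **1. The plan's own figure.** The only sample-size calculation is for work cessation: "We assumed 5 years of follow-up", "a rate of work cessation of 12.77% per year in the control group", "to detect a 35% relative risk reduction (HR = 0.65") and "80% power, a 2-tailed Cox model-based score test, equivalent to the logrank test, at alpha = 0.05".

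- Rate: −ln(0.60)/4 = 0.1277 per year.
- Five-year event probabilities: 1 − exp(−5 × 0.1277) = 0.472 in controls; 1 − exp(−5 × 0.1277 × 0.65) = 0.340 in the intervention arm; mean 0.406.
- Events: 4 × (1.960 + 0.842)² / (ln 0.65)² = 169.2, so 170.
- Participants: 170/0.4058 = 419, so 420 (210 per arm). With 20% loss, 210/0.8 = 262.5, so 263 per arm and 526 in total.

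The stated 420 and 526 are reproduced. Nothing comparable exists for WIS.

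**2. Inputs for the WIS check.** From the article: 526 participants, 12 strata, 1:1 allocation, permuted blocks of varying size. Assumed: block sets {2,4} to {4,6,8}; scores missing at random; incomplete cases dropped; fixed block effects; 80% power for the strata-only analysis.

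**3. How much is missing at 2 years.** The 20% loss is planned for the 5-year outcome. At a constant attrition rate, 2-year loss is 1 − 0.80^(2/5) = 0.085. I used 0%, 8.5% and 20%, plus 35% as a stress case.

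**4. Formula.** Treatment information is the sum over groups of n1·n0/(n1 + n0), where n1 and n0 are the observed numbers per arm. Groups are strata in one model and blocks in the other. With r the ratio of block to strata information, power ≈ Φ(2.80·√r − 1.96).

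**5. Results** (simulated permuted-block trials, averaged):

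| Missing | r, blocks {2,4} | r, blocks {4,6,8} | Power with fixed blocks (strata only = 80%) |
|---|---|---|---|
| 0% | 0.99 | 0.99 | about 79.5% |
| 8.5% | 0.94 | 0.97 | about 78% to 79% |
| 20% | 0.87 | 0.94 | about 74% to 78% |
| 35% | 0.77 | 0.89 | about 69% to 75% |

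Worked case, 20% missing and blocks {2,4}: 2.80 × √0.87 − 1.96 = 0.65, and Φ(0.65) = 0.74. Allowing for the fall in residual degrees of freedom (about 408 to 244 in this case) leaves the result at 74%. With 20% missing, about 44 of some 421 observed participants sit in single-arm blocks for {2,4}, and about 10 for {4,6,8}. Equal and skewed stratum sizes gave nearly the same ratios.

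**6. Validity and drift.** This was simulated at 20% missing for blocks {2,4} and {4,6}. Without drift, both analyses held the 5% level: 0.049 and 0.050 for {2,4}, 0.054 and 0.052 for {4,6}. With a linear drift of 2 SD over accrual, strata-only became conservative (0.029 and 0.025) while block adjustment stayed near nominal (0.056 and 0.045). Power then reversed: 70% with strata only against 75% to 76% with blocks. With a drift of 1 SD, the block model still lost 1 to 3 points.

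**7. Baseline WIS.** Adjusting for a covariate that correlates ρ with the outcome multiplies residual variance by about 1 − ρ². The article gives no ρ. The gain would match the block loss at r = 0.94 if ρ = √0.06 = 0.24, and at r = 0.87 if ρ = √0.13 = 0.36.

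**The case against.** The best case for the plan is that analysing as randomized is a recognized choice. It respects the allocation scheme and, as step 6 shows, keeps test size near nominal and gives more power under strong drift. A reader might infer that the block term buys nothing in validity and is simply a mistake. That inference fails. What remains is narrower: leaving blocks out did not inflate type I error in any scenario run, the reversal needed a 2 SD drift, and one calendar-time term addresses drift at far lower cost.

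The loss also depends on two choices that the article does not make. The wording permits a random block effect, which recovers between-block information. The intention-to-treat statement may imply imputation, which would keep blocks complete and the loss negligible. Both points stand, so the finding is conditional.

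The 80% starting power is assumed. The sample was set by the outcome needing the larger number, so WIS power may be higher. From 90%, ratios of 0.87 to 0.94 give about 86% to 88%.

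The 35% case applies the whole 5-year loss at year 2 and also assumes that WIS goes unscored after work stops. The plan's rate implies that 22.5% of controls and 15.3% of the intervention arm have ceased work by then (1 − exp(−2 × 0.1277) and 1 − exp(−2 × 0.1277 × 0.65)), but the article does not say that they have no WIS. Even granting that, scaled attrition leaves about 0.915 × (1 − 0.189) = 74% observed, so a 69% to 75% power figure should not be read as the expected result.

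Finally, participants in single-arm blocks are not excluded. Intention-to-treat concerns inclusion and allocated arm, not the weight that an observation carries, so the article does not contradict itself on this.

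**Conclusion.** The concern holds as a conditional inefficiency in the first primary analysis. It rests on fixed block effects, unimputed 2-year scores missing at random, blocks between {2,4} and {4,6,8}, little outcome variation between blocks, and 80% strata-only power. On those assumptions the cost is about 1 to 2 points of power at 8.5% missing, about 2 to 6 points at 20%, and next to nothing with complete data. The direction can reverse under strong accrual drift. The documents do not support calling it an invalid test, a contradiction or a departure from intention-to-treat.

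The part that does not depend on block details is the handling of baseline WIS. Making its inclusion conditional on observed imbalance, and expecting it to reduce power, forgoes precision that even a modest correlation would supply.

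**What to change.** Reword the primary WIS model under Sample size and analysis:

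- **Baseline WIS:** include it in all cases, not after inspecting for imbalance. This is a free improvement. The score is already among the baseline values to be inspected, and the change is wording only.
- **Design factors:** keep the 12 strata, or centre and arthritis type as factors.
- **Blocks:** drop the fixed block term. If drift over enrolment is a concern, enter block as a random effect or add calendar time of enrolment as one covariate, and say which. This is a cheap improvement. Its one downside is some loss of efficiency if strong drift occurs and neither term is included.

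No extra data or participants are needed. The change should be made before the 2-year scores are compared by arm.

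### The main 2-year WIS analysis leaves out baseline WIS unless the arms look different at baseline, and the protocol wrongly states that adjustment is likely to lower power

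*Protocol article*

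**What the plan says.** All of this stands in the protocol article under Sample size and analysis.

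- Lead model: "an Analysis of Variance (ANOVA) will evaluate the effect of the intervention on WIS measures at 2 years, adjusting for the 12 strata and blocking". Baseline WIS is not in it.
- Covariate adjustment: "We will also consider an Analysis of Covariance model after inspection of the baseline values in both treatment arms for factors such as WIS score". Disease duration, treating physician, age, gender and risk factors for work disability are candidates as well.
- Rule for entry: "If differences at baseline are observed, we will consider them as covariates". No threshold is given.
- Stated consequence: "Since the power of these analyses will likely be less than the original ANOVA, post hoc power analyses will be conducted", provided that the adjustments seem clinically meaningful.
- Before any of this, the outcome is tested for normality with the Shapiro-Wilk test: "If normality assumption is rejected, an appropriate transformation (e.g. such as logarithmic) will be employed".

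The only sample size derived in the article is for time to work cessation. For WIS the text says that power will be adequate, without giving a difference, a standard deviation or a correlation between baseline and 2 years.

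**The concern.** WIS is a continuous outcome measured on the same people at baseline and at follow-up. Its baseline value is normally among the strongest predictors of the later one. In a randomized comparison, putting it in the model removes between-person variance from the error term. That benefit does not depend on whether the arms look alike at baseline. The plan uses imbalance as the criterion for adjustment, although the reason to adjust is prognostic strength, and it describes adjustment as a likely loss of power.

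The article treats its other primary outcome differently. Its Cox model includes important predictors such as age, gender and disease duration in addition to any imbalanced factors, because leaving them out could pull the estimate toward the null.

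At stake is precision on the first primary outcome. It is also unclear which result counts if an adjusted analysis is run beside the ANOVA and the two disagree. Post hoc power would not settle that, because it adds nothing to the confidence interval.

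**Working it through.** **1. The plan's own figure.** Inputs: "We assumed 5 years of follow-up and a rate of work cessation of 12.77% per year in the control group"; a hazard ratio of 0.65; a two-sided test at the 5% level with power of 80%.

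- Hazard = −ln(0.6)/4 = 0.1277 per year.
- Five-year event probability: control 1 − exp(−0.1277 × 5) = 0.472; intervention 1 − exp(−0.1277 × 0.65 × 5) = 0.340; mean 0.406.
- Events (Schoenfeld) = 4 × (1.96 + 0.8416)²/(ln 0.65)² = 169.2, so 170.
- N = 170/0.4058 = 419, against the stated 420.
- Recruitment = 210/0.8 = 262.5, so 263 per group and 526 in total, as stated.

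The stated sample size reproduces. It says nothing about WIS, so the WIS steps below rest on assumptions.

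**2. Effect of adjusting for baseline WIS.** Let r be the correlation of baseline with 2-year WIS that remains after the strata, which the ANOVA already adjusts for. The document does not give r; 0.3 to 0.7 is assumed. Assume also that the ANOVA has 80% power with 210 per arm, which corresponds to a difference of 2.8016 × √(2/210) = 0.273 SD. Then:

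- residual variance under ANCOVA = (1 − r²) × that under ANOVA;
- power = Φ(2.8016/√(1 − r²) − 1.96);
- n per arm for 80% power = 210 × (1 − r²), rounded up.

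| r | 1 − r² | ANCOVA power | n per arm for 80% |
|---|---|---|---|
| 0.3 | 0.91 | 83.6% | 192 |
| 0.4 | 0.84 | 86.4% | 177 |
| 0.5 | 0.75 | 89.9% | 158 |
| 0.6 | 0.64 | 93.8% | 135 |
| 0.7 | 0.51 | 97.5% | 108 |

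**3. Other starting points.** If ANOVA power were 90%, replace 2.8016 by 1.96 + 1.2816 = 3.2416: ANCOVA gives 94% at r = 0.4 and 99.5% at r = 0.7. From 95% (1.96 + 1.6449 = 3.6049) it gives 98% and 99.9%.

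**4. When could adjustment lower power?** A noncentral t calculation charged degrees of freedom for 11 stratum terms and k covariates.

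- With r = 0, power goes from 79.8% to 79.7% for one covariate and to 78.8% for ten.
- With five covariates, of which only baseline WIS is prognostic, power is 82.9%, 89.4% and 97.3% at r = 0.3, 0.5 and 0.7.
- An observed imbalance of 2 standard errors adds d²/Sxx to the variance factor 2/n, where d is the baseline difference in SD units. Here d² = 4 × 2/210 = 0.0381 and Sxx is about 418, so the addition is 0.0000911 on 0.00952, or about 1%. Adjustment then gains once r² exceeds about 0.01, that is, r above about 0.10.

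**5. Adjusting only when baseline differs.** The rule has no threshold, so two were assumed: baseline p < 0.05 and p < 0.20. The simulation used 210 per arm, normal data and one baseline covariate, with 40,000 runs under the null and 20,000 under the 0.273 SD difference.

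| r | Power, always adjust | Power, adjust if p < 0.05 | Type I error, p < 0.05 rule | Type I error, p < 0.20 rule |
|---|---|---|---|---|
| 0.3 | 83.3% | 80.2% | 0.047 | 0.045 |
| 0.5 | 89.6% | 80.6% | 0.045 | 0.037 |
| 0.7 | 97.3% | 82.0% | 0.033 | 0.025 |

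The conditional rule stays close to ANOVA power and falls below the nominal 0.05.

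**The case against.** Several points on the other side are fair.

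- **Motive.** A reader might infer that ANCOVA is held back because it is thought to cost power. The text does not say so. The power sentence is the reason given for post hoc power analyses; the trigger for ANCOVA is an observed baseline difference. The power statement is wrong in itself, and nothing here depends on a motive.
- **Data-driven primary model.** A reader might also infer that the primary model is chosen after seeing the data and that false positives rise. The ANOVA is named as the lead model, and the ANCOVA is something the authors will also consider, most naturally as an additional analysis. Even if it replaced the ANOVA, the simulated rules make the test conservative.
- **Existing adjustment.** The ANOVA already adjusts for centre, arthritis type and blocking. The gain therefore depends on the correlation left after the strata, as assumed above.
- **Unknown starting power.** The 80% is assumed. The trial was sized on the outcome needing the larger sample, so WIS power may be higher and the gain in percentage points smaller. The proportional cut in variance is unaffected.
- **Normality test.** It is tempting to say that the Shapiro-Wilk test will almost always reject and that the log will fail. The article gives no WIS range, mean or standard deviation, and it names the log only as an example. That point is secondary and conditional.

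What remains is the omission of baseline WIS from the main model, the imbalance criterion, and a power statement in the wrong direction.

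**Conclusion.** The point holds in this limited form. The planned ANOVA is a valid test, but it is less efficient than it need be, and the protocol's statement about adjustment is wrong for any covariate set that includes a reasonably prognostic baseline score. The direction is secure once r exceeds about 0.10. The size is a range: from an assumed 80%, power rises by about 4 points at r = 0.3 and 18 points at r = 0.7, and by less from a higher start. The worst case, adjusting for covariates unrelated to the outcome, costs between 0.1 point (one covariate) and 1 point (ten). The consequence is lost power and an adjusted result whose standing is not fixed. The documents do not support a claim of inflated type I error.

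**What to change.** Make the primary WIS analysis one prespecified ANCOVA of 2-year WIS with arm, baseline WIS and the stratification factors already planned (centre and arthritis type), fitted whatever the baseline balance. Delete the imbalance trigger, the statement that adjusted analyses will likely have less power, and the post hoc power analyses; report the confidence interval instead.

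As a secondary change, analyse WIS on its original scale and do not let a Shapiro-Wilk test of the outcome decide on a transformation. With about 400 participants a comparison of means is robust to moderate non-normality. A log, if it were chosen, would be undefined for any zero score and would move the effect off the WIS scale.

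The cost is protocol and analysis-plan wording. WIS is already listed among the baseline values to be inspected, so no new data are needed, and the sample size does not change.

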In the analysis of our second primary outcome, time-to-event (survival) methodology will compare the risk of work cessation in the intervention and control groups. Subjects employed until end of their follow-up (study end, death or time of loss to follow-up, whichever occurs earlier) will be censored. First, Kaplan Meier ‘survival curves’ and logrank test will estimate and compare the proportions of subjects who continue being employed in the intervention and control groups. Next, multivariable Cox Proportional Hazards (PH) regression model [44] will be employed to estimate the adjusted Hazard Ratio (HR) with 95% CI, associated with the intervention after controlling for potential risk factors for WD that may be imbalanced at baseline, despite randomization, and for other important predictors, such as age, gender, RA duration at baseline, and physician providing RA care, whose omission could induce bias toward the null in time-to-event analyses [45]. We will use a flexible extension of the Cox model [46], which will allow us to estimate how the HR reduction due to intervention changes over time, if the proportional hazard assumption (that the intervention effect remains constant over time) is rejected.

For analyses of secondary outcomes, time-to-event methods will be employed for dichotomous outcome variables (e.g. time to temporary work cessation), and comparison of means between intervention and control groups will be employed for continuous variables (e.g. measures of absenteeism, job satisfaction, self-efficacy and risk factors for WD), as described above for the primary outcomes.

For the second primary outcome (time to work cessation), an interim analysis will be performed at 2 years of follow-up. We will use the same method as for the primary analysis and will employ the PETO criteria to adjust the overall type I error for multiple testing [47]. Specifically, we will use a conservative type I error of 0.001 for the interim analysis, which will allow us to maximize the power of the final analyses of the 5 year outcomes, which will employ the conventional 0.05 significance level.

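### The work-cessation analysis names neither randomization factor, lets baseline imbalance choose some Cox covariates, and does not say whether the logrank or the Cox result decides

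*Protocol article*

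**What the plan says.** **Randomization.** The article states: "Randomization will be stratified by study centre (3 levels) and type of arthritis (4 levels"). That makes 3 × 4 = 12 strata, with blocks inside each.

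**First primary outcome (Sample size and analysis).** The ANOVA of the WIS at 2 years is adjusted for those 12 strata.

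**Second primary outcome (Sample size and analysis).** Two steps are given.
- First, Kaplan-Meier curves and a test: "logrank test will estimate and compare the proportions of subjects who continue being employed in the intervention and control groups".
- Next, a multivariable Cox model with two groups of covariates. One group depends on imbalance: "controlling for potential risk factors for WD that may be imbalanced at baseline, despite randomization". The second group is an open list chosen for prognostic value: "other important predictors, such as age, gender, RA duration at baseline, and physician providing RA care". It is included because leaving such factors out could bias the result toward the null. A flexible Cox extension is added if proportional hazards is rejected.

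Centre and arthritis type are named in neither step. The Abstract mentions only the Cox model for this outcome, and ties the other predictors to baseline imbalance as well.

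**Sample size.** The trial is sized on "a 2-tailed Cox model-based score test, equivalent to the logrank test", with no strata or covariates mentioned.

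**Interim look.** At 2 years the method of the primary analysis is reused at a type I error of 0.001. Under Study design, a significant difference ends the trial early.

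**The concern.** Three things are fixed loosely for an outcome that can stop the trial.

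1. **Strata.** Blocking within strata makes the arms more alike on centre and arthritis type than chance would. If these factors predict work cessation, an unstratified logrank test uses a variance that is too large for the design, so it is conservative. The hazard ratio is also pulled toward 1 when a prognostic factor is left out. The article adjusts one primary outcome for the strata and does not mention them for the other.
2. **Covariates.** Some Cox covariates depend on which factors turn out imbalanced, with no list and no threshold, and the prognostic list is open. The adjusted hazard ratio is then not fully defined before the data are seen. The article's own reason for adjusting, to avoid bias toward the null, is about prognostic value, and chance imbalance is a poor guide to that.
3. **Deciding result.** The logrank test and the adjusted Cox model each give a p-value for the same outcome. The interim rule refers to the primary analysis without saying which of them it is.

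**Working it through.** **1. The plan's own figures.** Inputs from Sample size and analysis: "a rate of work cessation of 12.77% per year in the control group", read as an exponential hazard of 0.1277; 5 years of follow-up; "at alpha = 0.05, to detect a 35% relative risk reduction (HR = 0.65"); "A sample size of 420 subjects (210 per group) completing the study is necessary for 80% power"; 20% loss.

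- Hazard: −ln(0.60)/4 = 0.1277, matching 40% work loss over 4 years.
- Event probability at 5 years: control 1 − exp(−5 × 0.1277) = 0.4719; intervention 1 − exp(−5 × 0.1277 × 0.65) = 0.3397; mean 0.4058.
- Events (Schoenfeld): 4 × (1.960 + 0.842)² / (ln 0.65)² = 31.40 / 0.1856 = 169.2, so 170.
- N = 170 / 0.4058 = 418.9, against the stated 420. (Freedman's formula gives 175 events and 431, within 3%.)
- Power at 420: 420 × 0.4058 = 170.4 events; Φ(0.4308 × √170.4 / 2 − 1.960) = 0.803.
- Recruitment: 420 / 0.8 = 525, or 526 for equal arms.

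The sample size is reproduced. It is that of an unstratified, unadjusted test.

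**2. Effect of leaving the strata out.** The article gives no figure for how much work cessation differs between strata, so a range was simulated. Settings: N = 420; 12 strata (assumed shares: centres 40/20/40%, arthritis types 55/15/15/15%); permuted blocks of 2, 4 or 6; control work loss held at 40% over 4 years; 5 years of follow-up; 4,000 trials per cell. SD is the assumed between-stratum SD of the log hazard.

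| SD | Power, unstratified | Power, stratified | Difference | Type I error, unstratified | Type I error, stratified |
|---|---|---|---|---|---|
| 0 | 79.45% | 79.05% | −0.40 | 4.7% | 5.0% |
| 0.25 | 79.12% | 79.72% | 0.60 | 4.2% | 4.6% |
| 0.5 | 76.25% | 79.35% | 3.10 | 4.2% | 5.6% |
| 0.75 | 71.23% | 79.72% | 8.49 | 2.8% | 4.7% |

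The Monte Carlo standard error is √(0.8 × 0.2/4000) = 0.6 points for each power and √(0.05 × 0.95/4000) = 0.3 points under the null. A separate set with 526 participants, 20% exponential loss and 2,000 trials per setting agrees in direction. Power unstratified against stratified was 86.4% and 85.9% at SD 0, 81.2% and 82.8% at SD 0.4, and 75.0% and 80.0% at SD 0.7.

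To judge these SDs: the expected range of 12 normal values is about 3.26 SD, so the highest-to-lowest hazard ratio is typically about exp(3.26 × 0.25) = 2.3, exp(3.26 × 0.5) = 5.1 and exp(3.26 × 0.75) = 11.5.

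**3. Covariate rule and choice of test (illustrative).** Assumed: N = 420; 10 independent covariates with log hazard ratio 0.1, 0.2 or 0.3 per SD; 3 always in the model; 7 added only if imbalanced at p < 0.2. The overall event rate was not recalibrated as the covariate effects grew.

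- The imbalance-selected Cox model alone (3,000 trials per cell) held type I error at 4.6 to 5.1%. Its power was 79%, 77% and 73%, against 80%, 82% and 82% with all 10 covariates fixed in advance.
- Comparing only the two kinds of test that the article names (2,500 trials per cell), the unadjusted and the imbalance-selected result disagreed on significance in 5%, 10% and 17% of trials at HR 0.65. Under the null, counting either as success gave 5.9 to 6.6%. A repeat with another seed gave 5%, 10% and 16%, and 5.2 to 8.1%, with a standard error of about 0.5 points on each null figure.

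**The case against.** **A reader might infer that the strata are deliberately excluded.** The text does not say so. It is silent on whether the logrank test is stratified, and the words introducing the predictors leave that list open. A journal article may leave such detail to the full plan. This stands. What remains is an inconsistency within one section: the strata are written into one primary analysis and not the other.

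**A reader might infer that all Cox covariates are chosen by imbalance.** They are not. Age, gender, disease duration and physician are named for their prognostic value, and physician may partly stand in for centre. Only the risk factors for work disability depend on imbalance in Sample size and analysis, although the Abstract extends this to the other predictors.

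**A reader might infer that power is certainly lost or false positives inflated.** Neither follows. The loss depends on stratum effects that the article does not give, and the larger losses need hazards that differ several-fold between strata. Ignoring strata errs on the conservative side. Imbalance selection alone did not inflate type I error; only choosing between results did, and modestly.

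**Test, then estimate.** It is natural to read the logrank test as the comparison and Cox as the estimate, since the sample size rests on a logrank-equivalent test. This is plausible. But the article does not say it, and its Abstract gives only the Cox model.

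**A reader might take the RA covariates as undefined for the three other diagnoses.** This is loose wording. The paragraph on the WIS analysis speaks of disease duration in general.

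**Conclusion.** The point holds as a modest, nearly free improvement, and not as an error that invalidates the trial. The article is inconsistent in carrying the randomization strata into the WIS analysis while naming them nowhere for work cessation. It also states an imbalance-driven rule for part of the Cox model and leaves the deciding result unnamed at both looks.

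If the final test is in fact unstratified, the cost against a design power of 80% is about 0 to 1 point at a between-stratum SD of 0.25 or less, about 3 points at 0.5 and about 8 points at 0.75. Stratifying costs about half a point if the strata do not matter. These SDs and the stratum shares are assumptions. The figures for covariate selection and choice of test are illustrative only; their main message is that the two named results can disagree, and that nothing in the article says which then counts. The 420 and 526 need no change.

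**What to change.** - **Name one deciding analysis for both the 2-year and the final look:** a logrank test or a Cox model, stratified by or adjusted for centre and arthritis type, as the ANOVA already is. Say that the other result is supportive.
- **Fix the Cox covariates in advance on prognostic grounds,** for example age, gender, disease duration for the participant's own diagnosis, and baseline WIS. Keeping or dropping the physician factor is optional.
- **Move imbalance-driven adjustment to sensitivity analyses,** and bring the Abstract into line.

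The cost is wording only. Centre and arthritis type are known at randomization, and the example covariates already appear among the factors that the article plans to use. No participants or new data are needed. The change should be made before the 2-year look, because that look can end the trial.
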